### Ethics and dissemination

The trial was approved by the Independent Ethics Committee, First Affiliated Hospital of Fourth Military Medical University (ID: KY20150319, KY20150505-1) and was registered (registration date: 11 May 2015) in the United States National Institutes of Health Clinical Trials Registry (ClinicalTrials.gov, identifier: NCT02449603). The study will be supervised by Excellence Future International Consulting Co., Ltd. The findings of this trial will be submitted to a peer-reviewed journal. Abstracts will be submitted to relevant national and international conferences.

Each subject will provide signed and dated informed consent before conducting any procedure specifically for the study. Participation in this study is strictly confidential. Any information that is published will not reveal the identity of the subjects.

## Discussion

An unmet need exists for diabetes research with interest in glucose variability assessed by CGMS, as glucose variability is suggested to lead to the development of long-term complications [19] and MAGE assessed by CGMS is the “gold standard” to evaluate glucose variability.

In American Diabetes Association (ADA), European Association for the Study of Diabetes (EASD), and Chinese Diabetes Society (CDS) guidelines, both insulin and GLP-1 RA could be the initial option when oral therapies fail to provide adequate glycemic control, and nearly 70 % Chinese patients choose premixed insulin as the initial insulin therapy [4].

Previous studied have demonstrated that, compared with insulin aspart 30, exenatide showed a better effect on glycemic fluctuation assessed by seven-point SMBG with similar glycemic control and lower risk of hypoglycemic [16, 20]. For example, in a 52-week, open-label, non-inferiority trial, patients failing to reach treatment goals with metformin and sulphonylurea were randomized to exenatide (n = 253; 5 μg twice daily (BID) 4 weeks, 10 μg thereafter) or premixed insulin (n = 248; BID doses titrated for optimal glucose control). The results demonstrated that exenatide BID has a similar glycemic effect to insulin aspart 30 assessed with HbA1c in T2DM patients. More importantly, the results demonstrated that exenatide-treated patients had significantly greater reductions in postprandial glucose excursions (the difference between preprandial and postprandial plasma glucose levels) following the morning (*P* < 0.001), midday (*P* < 0.002), and evening meals (*P* < 0.001) than patients treated with premixed insulin assessed with seven-point SMBG [16]. However, in these studies, MAGE was not the primary endpoint, or CGMS was not used.

The statistically significant and clinically relevant reduction on glucose variability with exenatide was associated with the profile of safety and tolerability superior to biphasic insulin aspart 30. Data establishing the clinical efficacy of exenatide are based on two core Phase 3 studies: one glimepiride-controlled pilot study with glycemic variability assessed by CGMS, which only included 12 patients [17], and one biphasic insulin aspart 30-controlled study, where glycemic excursion was assessed by SMBG [16]. The key results of these studies were that treatment with exenatide resulted in consistent, clinically meaningful, and statistically significant greater reductions in glucose excursions, in addition to being associated with non-inferior glycemic control relative to the active comparator.

This is the first randomized controlled trial using CGMS to evaluate glycemic fluctuation between twice-daily exenatide and insulin aspart 30, which will provide beneficial evidence to exenatide usage in patients with T2DM.

### Trial status

This trial is currently ongoing and actively recruiting patients. The first participant was enrolled on 10 December 2015.

## Appendix 1

### Exclusion criteria

1. Women who are pregnant, intending to become pregnant during the study period, currently lactating females, or women of child-bearing potential not using highly effective, medically approved birth control methods.
2. Diagnosis or history of a) type 1 diabetes mellitus, diabetes resulting from pancreatic injury, or secondary forms of diabetes, for example, acromegaly or Cushing’s syndrome. b. Acute metabolic diabetic complications such as ketoacidosis or hyperosmolar coma within the past 6 months.
3. Previous treatment with any dipeptide peptidase-4 (DPP4) inhibitor or GLP-1 receptor agonists within the past year.
4. History of hypersensitivity reaction (for example, anaphylaxis, angioedema, or exfoliative skin conditions) to dipeptide peptidase-4 inhibitor (DPP4) or acarbose.
5. Treatment with any antidiabetic medication for more than 7 consecutive days other than metformin in the 3 months prior to screening.
6. Treatment with systemic glucocorticoids (oral or intravenous) for more than 7 consecutive days within the past 6 months.
7. Triglycerides (fasting) > 4.5 mmol/L (>400 mg/dL) at screening or within 4 weeks prior to screening (by local laboratory).
8. Patients with clinically apparent liver disease characterized by either of the following: a) ALT or AST > 3x upper limit of normal (ULN) confirmed on two consecutive measurements (by local laboratory) within 4 weeks prior to screening period; b) impaired excretory (for example, hyperbilirubinemia) and/or synthetic function, or other conditions of decompensated liver disease such as coagulopathy, hepatic encephalopathy, hypoalbuminemia, ascites and bleeding from esophageal varices; or c) acute viral or active autoimmune, alcoholic, or other types of hepatitis.
9. Patients with moderate/severe renal impairment or end-stage renal disease (estimated glomerular filtration rate ≤ 60 mL/min calculated by using the abbreviated equation developed by the Modification of Diet in Renal Disease (MDRD) study with modification for the Chinese population) at screening or within 4 weeks prior to screening (by local laboratory).
10. Congestive heart failure defined as New York Heart Association (NYHA) class III or IV.
11. Significant cardiovascular history within the 3 months prior to screening, defined as myocardial infarction, coronary angioplasty or bypass graft(s), valvular disease or repair, unstable angina pectoris, transient ischemic attack, or cerebrovascular accident.
12. History of chronic pancreatitis or idiopathic acute pancreatitis.
13. History of gastrointestinal disease, including gastroenterostomy, enterectomy, Roemheld Syndrome, severe hernia, intestinal obstruction, or intestinal ulcer.
14. History of genetic galactose intolerance, Lapp lactase deficiency, and glucose-galactose malabsorption.
15. History of medullary thyroid carcinoma.
16. Diagnosed and/or treated malignancy (except for basal cell skin cancer, in situ carcinoma of the cervix, or in situ prostate cancer) within the past 5 years.
17. History of organ transplant or acquired immunodeficiency syndrome (AIDS).
18. History of alcohol abuse or illegal drug abuse within the past 12 months.
19. Potentially unreliable patients and those judged by the Investigator to be unsuitable for the study.

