### Study population and eligibility criteria

A total of 150 subjects will be enrolled. Subjects should fulfil the following criteria:Provide informed consent prior to any study specific procedures.Men and women (nonpregnant and using a medically approved birth-control method) between 18 and 70 years of age at screening.Confirmed type 2 diabetes with history of at least half a year.Treatment with stable, maximum-tolerated doses of metformin (≥1500 mg/d, ≥ 3 months).HbA1c ≥ 7.5 % and ≤ 10.0 % at screening or within 4 weeks prior to screening (by local laboratory).Body mass index: 21 to 35 kg/m^2^.

Subjects should not enter the study if any of the exclusion criteria in Appendix 1 are fulfilled.

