### Interventions

The trial will include a 1-week screening period of stable doses of metformin (1500 mg) and a 16-week treatment period. Patient will take the first dose after randomization on Day 1. The investigational products of exenatide and biphasic insulin aspart 30 will be administered through subcutaneous injection. The background product of metformin will be taken orally at 500 mg three time daily until the completion of the study.

Exenatide (AstraZeneca) should be initiated, 60 minutes before breakfast and before dinner, at a low dose of 5 ug twice a day for 4 weeks and then titrated up to a standard dose of 10 ug twice a day until the completion of the study.

Biphasic insulin aspart 30 (Novo Nordisk) will be started at a dose of 0.2 to 0.4 IU/kg, or 10 to 12 IU/d, assigned to before breakfast or before dinner in a 1:1 ratio. The adjustment of the insulin dose will be instructed to achieve an optimal balance between glycemic control and the risk of hypoglycemia as dictated by clinical practice. It will be titrated to glucose targets of fasting plasma glucose (FPG) and predinner plasma glucose < 7 mmol/L. Insulin dose titration will be based on the average self-monitored blood glucose (SMBG) results for 3 days preceding visits, unless hypoglycemia occurs. If hypoglycemia occurs, titration will be temporarily postponed, and the reasons of hypoglycemia will be evaluated. Subjects could not increase the total daily dose by more than 10 U at any time. After visit 2 (week 0), insulin doses will be titrated weekly for the first 12 weeks, then every 2 weeks thereafter according to the titration algorithm (Table 1).

**Table 1 Tab1:** Prebreakfast and predinner insulin titration regimens

Fasting and/or predinner SMBG PG value (mmol/L)	Adjustment
<5.0	-2 U
5.0 to 7.0	No adjustment
7.1 to 7.7	+2 U
7.8 to 10	+4 U
>10	+6 U

BG, blood glucose; SMGB, self-monitored blood glucose

Glycemic targets for titration: Prebreakfast and predinner PG: 5.0 to 7.0 mmol/L. Prebreakfast dose of biphasic insulin aspart 30 is titrated based on the three mean predinner PG values for the 3 days prior to the visit. Predinner dose of biphasic insulin aspart 30 is titrated based on the three mean fasting PG values for the 3 days prior to the visit. The predinner biphasic insulin aspart 30 titration is not increased if the preceding day’s bedtime SMGB value is 5.6 mmol/L

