### Participant timeline

The time schedule for the enrollment, interventions, assessments, and visits for participants are shown in Table 3.

**Table 3 Tab3:** Study plan detailing the procedures

Study Period	Screening	Treatment							
Visit	V1	V2	V3	V4	V5	V6	V7	V8	V9
		Randomization							
Week	−1	0 (baseline)	1	2	4	8	10	12	16
Day		0	±2	±2	±7	±7	±2	±7	±7
Telephone visit			×	×			×		
Screening/baseline									
Written informed consent	×								
Inclusion/exclusion criteria	×	×							
Demographics	×								
Physical examination	×	×			×	×		×	×
Medical/current conditions	×	×	×	×	×	×	×	×	×
History of diabetes & complications	×								
Lifestyle instruction	×	×	×	×	×	×	×	×	×
Treatment									
Drug dispensing and accountability		×			×	×		×	
Concomitant medications	×	×	×	×	×	×	×	×	×
SMBG			×	×	×	×	×	×	×
Insulin titration			×	×	×	×	×	×	
Safety assessments									
Pregnancy test (urine)	×								×
Physical examination	×	×			×	×		×	×
Vital signs	×	×			×	×		×	×
12-lead ECG	×								×
Hematology panel	×								×
Urinalysis	×								×
Liver function	×								×
Creatinine, BUN, uric acid	×								×
Lipids	×				×				×
Adverse events		×	×	×	×	×	×	×	×
Efficacy assessments									
HbA1c	×								×
Fasting plasma glucose	×	×			×	×		×	×
Fasting insulin and C-peptide		×							×
CGMS		×							×
Standard meal test:2 h PPG, insulin and C-peptide		×							×
BW, BMI and WC	×	×			×	×		×	×
Other assessment									
MCP-1, hs-CRP		×							×
8-Iso-PGF2α		×							×
Urinary albumin		×							×

SMBG, self-monitoring of blood glucose; ECG, electrocardiogram; BUN, blood urea nitrogen; CGMS, continuous glucose monitoring system; PPG, postprandial plasma glucose; BW, body weight; BMI, body mass index; WC, waist circumference; MCP-1, monocyte chemotactic protein-1; hs-CPR, high-sensitivity C-reactive protein; 8-Iso-PGF2α, 8-Iso-prostaglandin F2α

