### Assignment of interventions

Patients will be randomized 1:1 to treatment groups via a central randomization system (interactive voice/web response system (IVRS/IWRS)), and the drug will be dispensed accordingly. The study population will be stratified at randomization based on MAGE (<5.6 mmol/l and ≥ 5.6 mmol/l) and the severity of the disease (HbA1c < 9.0 % and ≥ 9.0 %).

Because the study drug (Exenatide) has an obviously different appearance from, and is used differently from, the biphasic insulin aspart 30, a definite blindness is hard and worthless for investigators and patients. Therefore, an open-label study is being conducted. Bias at randomization is reduced by the use of a central randomization system. Moreover, key efficacy parameters (MAGE, HbA1c, FPG, and postprandial plasma glucose (PPG)) will be blinded for the investigator during the course of the study (from randomization to week 16) except for the screening and pre-randomization visit. However, when FPG meets the study drug discontinuation criterion of hyperglycemia, the investigator will be alerted to conduct retest for confirmation.

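### The only drug-hypersensitivity exclusion (Appendix 1, item 4) names DPP-4 inhibitors and acarbose, which the trial does not give, and omits exenatide and biphasic insulin aspart 30, which it does

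*Protocol article*

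**What the plan says.** The Interventions section of the protocol article identifies what patients are given: "The investigational products of exenatide and biphasic insulin aspart 30 will be administered through subcutaneous injection". Both are added to background metformin.

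The section on study population and eligibility criteria makes the appendix binding: "Subjects should not enter the study if any of the exclusion criteria in Appendix 1 are fulfilled". Appendix 1 lists 19 numbered exclusions. Item 4 is the one on drug hypersensitivity: "History of hypersensitivity reaction (for example, anaphylaxis, angioedema, or exfoliative skin conditions) to dipeptide peptidase-4 inhibitor (DPP4) or acarbose".

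Three other items bear on the point without mentioning hypersensitivity:

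- Item 3: "Previous treatment with any dipeptide peptidase-4 (DPP4) inhibitor or GLP-1 receptor agonists within the past year".
- Item 5: "Treatment with any antidiabetic medication for more than 7 consecutive days other than metformin in the 3 months prior to screening".
- Item 19: "Potentially unreliable patients and those judged by the Investigator to be unsuitable for the study".

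On allocation, the section on assignment of interventions states: "Patients will be randomized 1:1 to treatment groups via a central randomization system".

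**The concern.** A hypersensitivity exclusion exists to keep patients away from a drug they may be randomised to and have already reacted to. Item 4 is specific enough to give example reactions, but it attaches them to two drug types that nobody in the trial receives and leaves out both that patients do receive.

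Two things follow. A patient with a known reaction to exenatide or insulin aspart is not barred by any rule about hypersensitivity. And a patient who once reacted to acarbose or a DPP-4 inhibitor must be turned away although the trial would expose them to neither. What is at stake is patient safety and a needless exclusion. Item 4 acts before randomisation, so the comparison of change in MAGE is not biased by it.

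**Working it through.** The plan states no figure on this point, so the check is a reading of the eligibility rules against the drugs given, plus one line of arithmetic.

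**Drugs given (Interventions).** Exenatide or biphasic insulin aspart 30, with metformin in both arms.

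**Drugs named in item 4 (Appendix 1).** DPP-4 inhibitors and acarbose. The overlap with the drugs given is none. Acarbose appears nowhere else in the article.

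**Count over Appendix 1.**

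| Quantity | Count |
|---|---|
| Exclusion items | 19 |
| Items on drug hypersensitivity | 1 (item 4) |
| Items naming hypersensitivity to exenatide or biphasic insulin aspart 30 | 0 |

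The inclusion criteria do not mention hypersensitivity either. Item 14, the nearest other intolerance item, concerns sugar intolerance and malabsorption.

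**What other items cover incidentally.**

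| Past reaction to | Item that may apply | Covered | Not covered |
|---|---|---|---|
| Exenatide | 3 | Any GLP-1 receptor agonist treatment in the past year | Reaction after treatment more than 1 year ago |
| Insulin aspart | 5 | More than 7 consecutive days of use within the 3 months before screening | Exposure of 7 consecutive days or fewer, or earlier than those 3 months |

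Item 5 is a poor stand-in for a hypersensitivity rule, because a reaction is itself a reason to stop a drug early, and stopping within 7 days puts the patient outside the item. For everyone in the right-hand column, only item 19 remains, and it permits exclusion without requiring it.

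Metformin leaves no comparable gap: the inclusion criteria already require stable treatment for at least 3 months.

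**Chance of allocation to the drug concerned.** With a 1:1 ratio, the probability for a patient in the uncovered group who is entered is 1/(1 + 1) = 0.5. Allocation is central, so the site cannot choose the other drug.

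**How many patients.** The documents give no rate of earlier reactions to either drug, so no count can be derived and none is claimed.

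**The case against.** The strongest reply has four parts.

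- **The article condenses a fuller protocol.** That protocol may exclude hypersensitivity to the study drugs in words the article lost. This would carry weight if item 4 were absent or vague. But Appendix 1 is a full numbered list with laboratory cut-offs and look-back periods, the text does not call it abridged, and the hypersensitivity rule is present and detailed. It names the wrong drugs. If the full protocol reads differently, the published list still needs correcting.
- **In practice the risk is mostly handled.** Items 3 and 5 remove most recent users. Item 19 plainly lets an investigator refuse a patient with a known allergy to a study drug. Table 3 has the eligibility criteria checked at V1 and V2, and "Medical/current conditions" reviewed at every visit. For harm to occur, the reaction must be old or follow brief exposure, and it must then be missed or disregarded at two visits. This stands, and it is why the point is minor. It does not make item 4 correct: the plan chose to give hypersensitivity an explicit rule, so leaving the drugs actually used to discretion is not an adequate substitute.
- **The 0.5 is only the allocation ratio.** Correct. It is conditional on a patient having been entered and says nothing about how often that happens. The trial is also open-label, so an investigator who sees the allocation could withhold the drug; the cost might then be a withdrawal, not a re-exposure.
- **The over-exclusion is slight.** Also fair. It harms no enrolled patient, and nothing in the documents suggests that it affects recruitment.

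**Conclusion.** The concern holds, at minor severity. Item 4 is a binding rule that names two drug types the trial does not give and neither of the two it randomises. The uncovered group is narrow: reactions to exenatide more than a year old, and reactions to insulin aspart after 7 or fewer consecutive days of use or before the last 3 months.

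The effect is confined to safety and eligibility; sample size, power, alpha and analysis are untouched. The conclusion rests on reading Appendix 1 as the complete exclusion list, which is how the eligibility section presents it, and on counting insulin as an antidiabetic medication under item 5. Why those drugs were named cannot be established from the text, and the conclusion does not depend on it.

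**What to change.** Reword item 4 to exclude a history of hypersensitivity to exenatide, biphasic insulin aspart 30 or any of their excipients, and delete the reference to DPP-4 inhibitors and acarbose. Replacing the drug names is the essential change; the mention of excipients is a sensible addition but not needed to correct the error.

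The Trial status section says that recruitment is under way, so the allergy history of patients already enrolled should be checked once against the corrected wording. This matters less for patients already dosed, since Table 3 collects adverse events at every visit from V2.

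The cost is a one-line amendment to the eligibility list plus that single check. No new procedure is needed, because Table 3 already schedules the eligibility and medical-condition reviews at V1 and V2.

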## Abbreviations

ADA: American Diabetes Association
BG: blood glucose
BID: twice daily
BMI: body mass index
BUN: blood urea nitrogen
BW: body weight
CDS: Chinese Diabetes Society
CGMS: continuous glucose monitoring system
EASD: European Association for the Study of Diabetes
ECG: electrocardiogram
FAS: full analysis set
FPG: fasting plasma glucose
GLP-1RA: glucagon-like peptide-1 receptor agonist
hs-CPR: high-sensitivity C-reactive protein
IVRS/IWRS: interactive voice/web response system
LAGE: largest amplitude of glycemic excursion
LOCF: last observation carried forward
MAGE: mean amplitude of glycemic excursion
MCP-1: monocyte chemotactic protein-1
MODD: mean of the daily differences
PPG: postprandial plasma glucose
PPS: per-protocol set
SD: standard deviation
SMBG: self-monitored blood glucose
SS: safety analysis set
T2DM: type 2 diabetes mellitus
WC: waist circumference
8-Iso-PGF2α: 8-Iso-prostaglandin F2α
